## **8.8. Definition of terms**

### **8.8.1. Medication adherence**

- The extent to which patients take their medications as prescribed with respect to dosage and dosage intervals throughout the treatment period

### **8.8.2. Effectiveness**

- The ability of a digital health intervention to achieve the intended results

### **8.8.3. Cost-effectiveness**

- Comparison of two alternatives where consequences of the intervention are measured in natural units

### **8.8.4. Usability**

- the capability in human functional terms to be used easily and effectively by the specified range of users, given specified training and user support, to fulfill the specified range of tasks, within the specified range of environmental scenarios.

### **8.8.5. TB patient**

- An individual diagnosed with active TB disease (pulmonary or extrapulmonary).

### **8.8.6. TB patient cost**

- Survey of costs faced by TB-affected patients and their households.

#### **8.8.7. New cases**

- A newly registered episode of TB in a patient who has never been treated for TB or has taken anti-TB medicines for less than 1 month.

#### **8.8.8. Bacteriologically confirmed TB case**

- A patient from who has at least one positive result either by smear microscopy, culture or Xpert MTB/RIF assay.

#### **8.8.9. Loss to follow-up**

- Patients have previously been treated for TB and were declared lost to follow-up at the end of their most recent course of treatment and are now diagnosed with TB.

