**Intervention:** Participants will be randomly assigned (1:1) to receive a 15-day TB medication supply in the evriMED500® MERM device to self-administer and return every 15 days (intervention arm) or the standard in-person DOT (control arm). Both will be followed throughout the standard two-month intensive treatment phase (2RHZE). The MERM device has an electronic module and a medication container that records adherence, stores medication, emits audible and visual on-board alarms to remind patients to take their medications on time and refill, and enables providers to download the data and monitor adherence.

**Study Duration:** The study duration is 12 months from opening enrollment until completion of data analyses. Participant duration is 2 months for each individual participant to complete all visits.

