### **6.2.2. Adverse treatment outcome**

- Participants having at least one of the three events: treatment not completed; death; or loss to follow-up.

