#### **8.5.1.2. Inclusion criteria**

Inclusion criteria will include:

- Patients with new, or previously treated, bacteriologically-confirmed drug-sensitive pulmonary TB
- Eligible to start the standard 6-month first-line anti-TB medication
- Outpatient status at the time of screening and enrollment
- Men or women age  $\geq 18$  years
- Able and willing to provide informed consent

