#### **8.8.10. Treatment completed**

- A TB patient who completed treatment without evidence of failure BUT with no record to show that sputum smear or culture results in the last month of treatment and on at least one previous occasion were negative, either because tests were not done or because results are unavailable.

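### The adverse treatment outcome counts loss to follow-up, but the protocol defines that term as a pre-enrolment history, gives the outcome no time window, and does not say how patients with documented negative sputum are classified.

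*Protocol*

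**What the plan says.** Section 6.2.2, repeated in the synopsis, defines the outcome as "Participants having at least one of the three events: treatment not completed; death; or loss to follow-up". It gives no time window and does not refer to any definition of its components.

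The components are described only in Section 8.8, Definition of terms:

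- Loss to follow-up (8.8.9): "Patients have previously been treated for TB and were declared lost to follow-up at the end of their most recent course of treatment", ending "and are now diagnosed with TB".
- Treatment completed (8.8.10): the wording is "completed treatment without evidence of failure BUT with no record to show that sputum smear or culture results in the last month of treatment". The record that must be lacking is one of negative results both then and at some earlier time, whether because no test was done or because no result is available.

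The inclusion criteria (8.5.1.2) admit "Patients with new, or previously treated, bacteriologically-confirmed drug-sensitive pulmonary TB" and require that participants be "Eligible to start the standard 6-month first-line anti-TB medication". The synopsis states "Participant duration is 2 months for each individual participant to complete all visits". Section 8.5.1.3 places the final study visit at month two. Section 8.7 has the case report form on overall treatment outcomes filled in from registers and charts at the end of the intensive phase. Section 8.6 puts both arms on standard DOT for the remaining four months and mentions no study follow-up in that period.

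**The concern.** A composite is only as good as the rules for its components, and three things are fixed badly here.

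First, 8.8.9 describes something that happened in an earlier course of treatment. As an outcome rule, it records an event for people who arrive with that history and records none for people who drop out of care after randomisation.

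Second, the outcome does not say over what period treatment must be completed.

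Third, 8.8.10 separates patients who finished treatment without bacteriological proof from those with proof, usually called cured. Section 8.8 does not define *cured*, and 6.2.2 does not say that such patients count as having completed.

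This composite is the listed outcome that counts death, loss and non-completion. A comparison of self-administered with observed therapy needs these events counted in the same way in both arms. The trial is open-label with ten sites, so an unclear rule leaves the classification to whoever abstracts the record.

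**Working it through.** **The plan's own figure.** The protocol makes no calculation for this outcome. Its only design calculation (8.5.1.5) concerns adherence: SD 36, margin 20, true difference 0, one-sided 2.5%, power 80%.

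n per arm = 2 × [36 × (1.960 + 0.842) / 20]² = 50.86, rounded up to 51. With 10% attrition, 51 / 0.90 = 56.7, rounded up to 57 per arm and 114 in total. This reproduces the protocol's figure, and nothing in this point changes it.

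**Loss to follow-up.** There are four kinds of participant. The table compares 8.8.9 as written with loss during the trial, for this component only.

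| Participant | Event under 8.8.9 | Lost during the trial |
|---|---|---|
| No earlier loss, retained | No | No |
| No earlier loss, lost on study | No | Yes |
| Earlier loss, retained | Yes | No |
| Earlier loss, lost on study | Yes | Yes |

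Rows two and three are wrong. In row four the answers agree, but only because of the history. A row-two participant may still enter the composite as *treatment not completed*, if that component is applied in its plain sense. A row-three participant enters the composite falsely whatever happens on study.

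**Size.** The protocol does not say how many participants will have been lost in an earlier course, so the number in row three is unknown. With 57 per arm, each wrongly classified participant changes that arm's rate by 1/57 = 1.75 percentage points. Randomisation makes the history equally likely in the two arms on average. Its main effect is therefore to add events unrelated to the intervention, plus whatever chance imbalance arises.

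**Window.**

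- Treatment length: 6 months (8.5.1.2).
- Study follow-up and outcome form: month 2 (synopsis, 8.5.1.3, 8.7).
- Treatment remaining: 6 − 2 = 4 months, matching the continuation phase in 8.6.

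Completion of the course, and any death or loss in those four months, lies outside the observed period. The adherence outcome (6.1.1) and the cost outcome (6.2.6) are expressly limited to the two-month intensive phase. Section 6.2.2 is not.

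**Treatment completed.** To fall outside 8.8.10 on sputum grounds, a patient needs negative results on record both in the last month and on a previous occasion. Section 8.3 uses the word differently. Of 2,290 cases it reports 1,811 completed and 1,526 cured. Since 1,811 + 1,526 = 3,337 exceeds 2,290, the two groups overlap there. The protocol thus uses *completed* in two senses, and 6.2.2 does not say which applies.

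**The case against.** Section 8.8 reads as a general glossary. Its entry for a TB patient includes extrapulmonary disease, although concurrent extrapulmonary TB is an exclusion. Section 6.2.2 does not cite 8.8.9 or 8.8.10. Outcomes will be abstracted from TB registers and charts, where staff may apply sensible categories. The two-month design is consistent throughout, so completion of the intensive phase is a natural reading. An analysis plan may also set out how the composite is derived.

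Part of this stands. The data source is named, and the team may well intend the sensible meaning. But 8.8.9 is the only meaning the protocol gives for a term used in an outcome, and no reading turns it into an on-study event. An analysis plan would have to contradict the protocol to put it right.

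A reader might go further and infer that nearly every participant would be classed as adverse. Taking *not completed* as everyone outside 8.8.10, and assuming that all cured patients in 8.3 are counted within completed, gives (2,290 − 285)/2,290 = 87.6%, where 285 = 1,811 − 1,526. Taking the month-2 cut-off literally gives 100%. The documents support neither figure. Section 6.2.2 does not define non-completion as the complement of 8.8.10. The two figures also rest on incompatible readings: full-course outcomes known in one, unobservable in the other.

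Within the trial's own window, 8.8.10 would exclude few participants. Study sputum is taken before and after the intensive phase and entry requires bacteriological confirmation, so a participant who is positive at entry and negative at month 2 has only one negative result. Someone positive on Xpert but smear-negative at entry would be an exception.

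**Conclusion.** The point holds as a defect in the definition of one secondary outcome. Loss to follow-up is defined by a history before enrolment, the observation window is not stated, and the status of participants with documented negative sputum is left open. The first defect is the clearest, because the stated rule gives the wrong answer for identifiable participants. Its size cannot be estimated from the protocol beyond about 1.8 percentage points per misclassified participant in an arm of 57. The conclusion assumes that Section 8.8 supplies the meaning of terms used in Section 6, since the protocol offers no other.

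A reader might infer that the trial could not show clinical failure or harm from reduced supervision. That does not follow. Sputum conversion is a primary outcome, recorded adherence and the urine isoniazid test are also compared, adverse events are to be reported, and death is untouched by either definition. The primary outcomes and the sample size of 57 per arm are not affected.

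**What to change.** Make three changes to the wording of 6.2.2 and 8.8:

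1. For outcome purposes, replace 8.8.9 with loss to follow-up that occurs after randomisation, as recorded in the TB register. If the existing text is needed to describe patients at entry, keep it under a label that marks it as a registration category.
2. State that the composite runs from randomisation to the end of the intensive phase and consists of death, on-study loss to follow-up, or intensive phase not completed.
3. State that documented negative sputum does not make a participant *not completed*.

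These changes cost only wording. They need no new data source, no extra visits and no change to the sample size. If the sponsor wants a full-course outcome instead, the protocol should say so and provide for register abstraction at month 6 in both arms, which is a modest extra data-collection task.

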#### **8.8.10. Treatment completed**

- A TB patient who completed treatment without evidence of failure BUT with no record to show that sputum smear or culture results in the last month of treatment and on at least one previous occasion were negative, either because tests were not done or because results are unavailable.

#### **8.8.11. Healthcare facility**

- Any establishment of facility (public or private) that is engaged in direct care of patients on site.

### **8.9. Data management**

The study will use a password-protected offline Research electronic data capture (REDCap) database, Vanderbilt University, United States to enter data and store entered data in an encrypted drive. The Principal Investigator will keep the source data in a locked cabinet at the study's central office. The assigned study staff will check a random sample of 10% of all data entry forms for entry errors.

## **9. STATISTICAL ANALYSIS**

Descriptive summary measures will be used to report participant characteristics. Chi-square tests will be used to evaluate potential associations among categorical variables. To compare the level of adherence between study arms and among variables, independent t-tests will be done on log-

transformed adherence percentage of the expected 60 days. Effects of the arms and other adherence variables will be estimated using a geometric mean (GM) with geometric standard deviation (GSD) and mean ratios (MR) with 95% confidence intervals (CI). Log binomial regression will be conducted to identify risk factors of at least one negative isoniazid urine test and self-reported adherence of participants. Effects will be measured using adjusted relative risk (ARR) with 95%CI. A general linear model will be done on log-transformed adherence percentage to identify the effects of variables on participants' level of adherence. Effects will be measured using an adjusted mean ratio (AMR) with 95% CI.

Descriptive statistics including frequency and percentage will be used to describe the health state of the study participants. Multiple bar charts with cross-tabulation will be used to illustrate distributions of health states by study arms. Chi-square and Fisher's exact tests will be employed to compare the five EQ-5D-5L health domains by study arms. Kolmogorov–Smirnov, Shapiro–Wilk tests, and median values with interquartile range (IQR) will be used to summarize EQ-5D-5L index value/utility. Nonparametric Mann–Whitney U test will be employed to compare the difference in EQ-5D-5L index value/utility among study arms. A log-binomial model will be used to identify risk factors for lower HRQoL, which is having at least one health problem.

The overall TB treatment cost will be estimated by considering costs related to anti-TB drug pick-up, guardian costs, and coping costs over the two-month intensive phase. The proportion of study participants who faced catastrophic costs at a cut-off point of 20% will be estimated. A cross-tabulation will be employed to evaluate the distribution of catastrophic cost over the study arms and chi-square test will be used to test the association between catastrophic cost and study arms.

To compare the TSQM scores between study arms, independent t-tests will be done on log-transformed scores. Effects of the arms will be estimated using a geometric mean (GM) with geometric standard deviation (GSD) and mean ratios (MR) with 95% confidence intervals (CI). A general linear regression will be done on log-transformed TSQM scores to identify the effects of variables on participants' level of satisfaction. Effects will be measured using an adjusted mean ratio (AMR) with 95% CI. In all analyses, a 5% significance threshold will be used to determine statistical significance.

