#### **8.5.1.5. Sampling and sample size**

The sample size is calculated considering a 1-sided type I error of 2.5%, a power of 80%, 10% attrition rate, delta of 20%, non-inferiority margin, and a continuous outcome of percentage adherence over the two-month intensive phase, with a standard deviation of 36% and 79% of average adherence, assuming null hypothesis for both arms. The results yield a sample size of 57 in each arm for a total of 114 participants. We will do a  $\log_{10}$  transformation on the data, where a difference can be equivalently transformed into a ratio using a power ( $10^3$ ). The non-inferiority will be calculated as the log in the control minus the log in the intervention, which is equivalent to the log of the control divided by intervention.

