### **8.6. Interventions**

Participants in the intervention arm will receive a 15-days TB medication supply (HRZE fixed-dose combination therapy of 15 doses) in an electronic pillbox device (evriMed500 digital medication monitoring and reminder device manufactured by Wisepill Technologies, South Africa) to self-administer. Providers will collect baseline data, including demographic, socioeconomic, behavioral, and social factors using the study's baseline questionnaire. Based on the baseline data, participants will be clustered into four behavioral determinants (use cigarettes, alcohol, Khat - a psychostimulant plant, and cocaine/marijuana) and three social determinants (homeless, unemployed, and illiterate) as appropriate for the purpose of analysis. Participants in this arm will return every 15 days, where the provider will count any remaining tablets in the pillbox, download the pill-taking data from the Wisepill device, evaluate the functionality of the device and troubleshoot as needed, and perform the urine

isoniazid test. The level of adherence in their intensive phase of treatment will be calculated using the medication possession ratio (MPR). Any participant who misses more than five tablets in any 15- day refills will be reassigned to daily DOT throughout the remaining days of the intensive phase. Participants in the intervention arm can consult the healthcare provider in cases of medical illness or any adverse events outside of a scheduled visit before the next appointment. The phone number of the healthcare provider following their TB condition will be written at the backside of their appointment cards. The phone call strategy aims to maintain the DOT advantage for the intervention arm.

Participants in the control arm will get their treatment as per the standard practice of DOT, where participants will visit the healthcare facility each business day throughout the two months intensive phase to swallow their daily dose of HRZE with direct observation by the healthcare provider. Additionally, they will be given pills for the weekend to take them at home. The provider will collect baseline data, conduct a urine isoniazid test every 15-days, and cluster participants into behavioral and social determinants as applicable for participants in the intervention arm. For this arm, the management of participants who interrupt treatment will follow the national TB treatment guidelines.

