## **8.7. Study procedure**

The main data collection tools will include

- a baseline patient information questionnaire (demographic, socioeconomic, behavioral, social, and clinical information),
- medication adherence measurement tools (MERM vs. DOT daily treatment adherence monitoring tool and urine colorimetric isoniazid test - IsoScreen™ test, GFC Diagnostics Ltd, Bicester, England, and adherence self-report questionnaire),
- clinical measurement tools (pre-post treatment sputum Xpert MTB/RIF assay or microscopy and adverse treatment outcome monitoring tool),
- cost/economic tools (health-related quality of life [HRQoL], catastrophic cost, post-diagnostic cost from an individual patient's perspective, predictors of HRQoL and catastrophic costs,

- Usability and treatment satisfaction tools (treatment satisfaction questionnaire for medication version 1.4 (TSQM v1.4) tool and an 18-item treatment satisfaction questionnaire)

The study investigators will identify healthcare providers in the TB clinics and provide training on the study procedures, how to operate the evriMED500 device, and perform a urine isoniazid test. The investigators will perform a 1:1 randomization of participants before the start of the study using computer-generated random numbers. Providers will enroll participants in the two arms sequentially as they arrive in the clinic and the investigators will routinely monitor the process. Providers will provide instruction using the Amharic version of the study's participant information sheet. Providers will recruit participants and obtain written informed consent in the local language, which is Amharic. The consent form will also function as an acknowledgment of personal responsibility keeping the device properly and returning upon completion of the study.

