For the laboratory research involving biological specimens (urine and sputum), the study will use WHO-approved diagnostic tools. The IsoScreen test is a semi-quantitative urine test that provides a reliable and immediate indication of adherence to isoniazid-containing treatment regimens for patients with TB. It uses the reagents of the Arkansas Method: barbituric acid (20 mg), potassium cyanide (10 mg) and chloramine-T (10 mg), in an enclosed plastic testing device for safe and rapid testing in clinics and patients' homes. A urine sample is added to the plastic testing device. If the sample develops a blue color, it is positive for isoniazid metabolites and is therefore from a patient who is compliant with the treatment. A blue/purple color indicates that the drug was taken within the last 24 hours. A green color

also indicates isoniazid metabolites, but the drug was probably taken about 48 hours ago. If the sample remains yellow, then the patient is not adhering to their daily treatment. The providers will perform this test within the study facilities for both arms every 15 days, thus four times per participant. Sputum specimens collected before and after the intensive phase. Under the routine practice, the sputum samples will be tested for Acid-fast bacilli (AFB) microscopy to check for sputum smear conversion following the intensive phase. Initiation, termination or completion of treatment will rely only on the standard procedures available at the study sites, which could be acid-fast bacilli or Xpert MTB/RIF assay. Thus, the outcomes of the study's laboratory results will not dictate the standard diagnostic or treatment procedures.

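### Catastrophic cost is compared by an unadjusted chi-square although baseline employment is recorded for analysis, and the only method covering sputum conversion gives no arm difference with a confidence interval

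*Protocol*

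**What the plan says.** **Catastrophic cost.** Sections 1.1 and 6.2.5 define it as treatment cost of at least 20% of income. Section 9 says the proportion affected will be estimated and cross-tabulated by arm, and that a "chi-square test will be used to test the association between catastrophic cost and study arms". No adjusted model is given, although the tool list in Section 8.7 includes predictors of catastrophic cost.

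**Sputum conversion.** This is a primary outcome (Section 6.1.2). Section 9 does not name it. The one stated method that could apply is the general sentence "Chi-square tests will be used to evaluate potential associations among categorical variables".

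**Baseline data.** Section 8.6 states: "Providers will collect baseline data, including demographic, socioeconomic, behavioral, and social factors". It then groups participants in both arms by social determinants (homeless, unemployed, illiterate) so that the grouping can be used in analysis. Section 8.7 adds: "Sputum specimens collected before and after the intensive phase". The baseline test may be Xpert or microscopy.

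**Randomisation.** "The investigators will perform a 1:1 randomization of participants before the start of the study using computer-generated random numbers". No stratification factor is stated.

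**Hypothesis.** Section 4 states non-inferiority for both adherence and treatment outcomes.

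**The concern.** There are two separate weaknesses.

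First, catastrophic cost is defined relative to income, so employment status at entry is a natural prognostic factor. The protocol collects it and earmarks it for analysis, but the only stated arm comparison for this outcome ignores it. Nothing in the stated randomisation balances it either. Whatever part of the outcome variance it explains stays in the error of the arm comparison.

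Second, a chi-square test of association yields a p-value for the hypothesis of no association. A non-inferiority claim needs an estimated arm difference and a confidence limit. A non-significant chi-square in a trial of this size could be mistaken for support of non-inferiority on a primary outcome. Adherence and treatment satisfaction do get an arm effect with a confidence interval in Section 9 (mean ratios); sputum conversion and catastrophic cost do not.

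**Working it through.** **1. The plan's own sample size.** Section 8.5.1.5 uses a "1-sided type I error of 2.5%, a power of 80%, 10% attrition rate, delta of 20%, non-inferiority margin", "with a standard deviation of 36% and 79% of average adherence, assuming null hypothesis for both arms".

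n per arm = 2 × [36 × (1.960 + 0.842) / 20]² = 50.86, so 51. With 10% attrition, 51 / 0.9 = 56.7, so 57. This matches the protocol: "The results yield a sample size of 57 in each arm for a total of 114 participants". About 51 per arm (102 in total) are expected to be evaluable. This sizing is for adherence only; none is given for sputum conversion or catastrophic cost.

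**2. General effect of adjustment.** Adjusting for a baseline predictor that explains a share R² of the outcome variance multiplies the variance of the risk difference by about (1 − R²). The protocol gives no R², so a range is shown.

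| R² | Fall in SE, 1 − √(1 − R²) | 102 act like 102 / (1 − R²) |
|---|---|---|
| 0.05 | 2.5% | 107 |
| 0.10 | 5% | 113 |
| 0.20 | 11% | 128 |
| 0.30 | 16% | 146 |

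A simulation with 51 per arm and logistic standardisation agrees: SE ratios of 0.97, 0.90 and 0.85 at R² of 0.07, 0.18 and 0.30.

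**3. Catastrophic cost, one assumed scenario.** Suppose 35% of participants are in a disadvantaged group with risk 60%, and the rest have risk 15%. None of these figures is in the protocol.

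- Overall risk: 0.35 × 0.60 + 0.65 × 0.15 = 0.3075; variance 0.3075 × 0.6925 = 0.2129.
- Explained: 0.35 × 0.65 × 0.45² = 0.0461. R² = 0.0461 / 0.2129 = 0.22.
- Simulated variance ratio, Mantel-Haenszel to crude: 0.79, worth 1 / 0.79 − 1, or about 26% more participants.
- 95% half-width: 1.96 × √(2 × 0.2129 / 51) = 17.9 points crude; 17.9 × √0.79 = 15.9 points adjusted.

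A weaker predictor gives much less. At R² of 0.05 to 0.10 the same crude half-width falls only to 17.5 to 17.0 points.

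**4. Sputum conversion, one assumed scenario.** Suppose four baseline categories with shares 15/30/25/30% and conversion 97/93/87/72%, again not from the protocol.

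- Overall conversion 85.8%; variance 0.858 × 0.142 = 0.1218; explained variance 0.0092; R² = 0.075.
- Simulated SD of the difference: 0.0689 crude, 0.0675 Mantel-Haenszel. The variance falls by about 4%, less than R² suggests because four strata in 51 per arm are thin.
- 95% half-width: 1.96 × 0.0689 = 13.5 points, against 1.96 × 0.0675 = 13.2 points.

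**5. Chance imbalance.** For a factor with 30% prevalence and 57 per arm, the SD of the arm difference is √(2 × 0.3 × 0.7 / 57) = 8.6 points, and a gap of 10 points or more occurs in about 24% of trials. In the scenario of step 4, conversion is 72% in the heaviest category and about 92% otherwise, so a 10-point gap moves the crude difference by about 0.10 × 20 = 2 points. Over repeated randomisations these shifts average out: the simulated bias of the crude difference was within 0.2 points.

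**The case against.** **Covariates belong in the SAP, and Section 9 does not name sputum conversion.** This stands in part. It cannot be said that the protocol fixes a crude chi-square for sputum conversion, and an unseen SAP may specify more. What can be said is that the only stated method able to cover this primary outcome does not produce the quantity its hypothesis needs. For catastrophic cost the test is stated outright.

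**The two outcomes are not singled out.** This also stands. The stated arm comparisons for adherence and satisfaction are t-tests, and for the EQ-5D index a Mann-Whitney test. The regressions in Section 9 are described as a search for risk factors or effects of variables, not as the main arm comparison. A reader might infer that every other outcome has an adjusted arm comparison as its main analysis; the text does not say so.

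**The strongest predictors may not be collected.** A reader might infer from the pre-treatment sputum sample that a graded smear is available for everyone. The protocol never mentions smear grade, allows Xpert at baseline, and admits patients confirmed elsewhere. Adjustment for sputum must therefore depend on what is recorded.

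**Income is a hazardous stratum.** Correct. Baseline income is not named, and costs are assessed at the end of the intensive phase (Section 8.7). Section 2.1 describes patients losing jobs and income because of daily attendance. Income known only at that point may be affected by arm, and it is also the denominator of the outcome. Baseline employment avoids this.

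**Chance imbalance does not invalidate a randomised comparison.** Correct. A reader might infer bias from the 24% figure; steps 4 and 5 show a shift of about 2 points inside a half-width of 13.5, already carried by the crude interval.

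**Conclusion.** The point holds, mainly for catastrophic cost. There the protocol fixes an unadjusted test, and a relevant baseline factor is already recorded in both arms for analysis. The gain ranges from a 2.5% smaller SE at R² 0.05 to 16% at R² 0.30. It is material (102 evaluable participants acting like 128 or more) only if employment and related factors explain about 20% or more of the variance, which the protocol neither supports nor rules out.

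For sputum conversion the precision gain is probably small: about 4% of variance under the assumed mix. The stronger defect is that a test of association gives no arm difference with a confidence interval for a non-inferiority hypothesis on a primary outcome.

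The crude comparison is valid and unbiased. The case is for a better-specified analysis; the planned one would not mislead through imbalance. All rates and R² values are assumptions; only the 57 per arm and the inputs behind it come from the protocol.

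**What to change.** In Section 9, or in the SAP before the data are seen:

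- **Catastrophic cost.** Make the main analysis the arm risk difference with 95% CI, stratified by or standardised over baseline employment status (Mantel-Haenszel or logistic standardisation). State that income measured at the end of the intensive phase will not be used as a stratum. Keep the chi-square as supportive.
- **Sputum conversion.** Name the outcome and report the arm risk difference with 95% CI. Adjust for the pre-treatment sputum result category if it is recorded for all participants; otherwise report the unadjusted difference with its CI. Use few categories, because thin strata at 51 per arm lose part of the gain.

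The interval for sputum conversion also needs a margin to be read against. The only margin in the protocol is the one used to size adherence.

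The cost is wording. No participants are added and N stays at 114. No new data are needed for employment; for sputum this depends on what the sites record. The one small downside is that the strata must be named in advance.
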